##### Pain self-efficacy questionnaire (PSEQ-2)

PSEQ-2 is a two-item questionnaire that rates pain self-efficacy, which is defined as the confidence held by people living with chronic pain that they can participate in certain activities and enjoy life, despite the pain they experience [24, 25]. The self-efficacy in each question is rated on a numerical rating scale (0–6 where 0 = not at all confidence and 6 = completely confidence).

##### Pain catastrophising scale (PCS-6)

PCS-6 is a six-item questionnaire designed to monitor catastrophising thinking, in a rating scale from 0 to 4 [26, 27]. Pain catastrophising implies the negative cognitive-affective reply to pain and is correlated with pain severity, disability, and depressive symptoms as well as with inadequate adjustment to chronic pain [28, 29].

##### Patients’ global impression of change (PGIC)

PGIC is a single-item questionnaire used for the identification of a significant clinical change by rating the participant’s belief about the treatment’s effectiveness on a 7-point rating scale (1–7, where 1 = no change and 7 = a great deal better).

##### Additional measurements

In addition to the aforementioned questionnaires, the participants will be asked to provide background information about themselves, such as age, gender, type and dose of medication, date of amputation, amputation cause, type and usage of prosthesis, and previous treatments. Furthermore, an additional survey will be conducted regarding the participants’ expectancy of benefit by using the expectations for complementary and alternative medicine treatments (EXPECT-SF) [30]. Moreover, the participants will be asked to participate in brief, semi-structured interviews in order to understand how the participants have experienced the treatment and how it has affected their quality of life. See Table 3 for a summary of all study-specific assessments at each visit.

**Table 3 Tab3:** Summary of study-specific assessments at each study-specific session

Session	Assessments
**Pre-screening**	• Patient information • Study consent • Background information
**Screening, visit 0**	• Pain survey • PDI • EQ5D-5L • PSEQ-2 • PCS-6 EXPECT-SF
**Baseline, visits 1–3**	NRS (0–10); RLP, neuroma pain, PLP
**Randomisation, allocation 1:1:1**	
**Surgery, visit 4**	• Surgery
**Follow-up, visits 5–10**	• Pain survey • PDI • EQ5D-5L • PSEQ-2 • PCS-6 • PGIC • Interview (visit 8)
*Short-term*	
1 month	
3 months	
6 months	
12 months	
Unblinded	
*Long-term*	
2 years	
4 years	

*PDI* Pain disability index, *EQ5D-5L* EuroQol-5D-5L, *PSEQ-2* Two-item Pain Self-Efficacy Questionnaire*, PCS-6* Six-item pain catastrophising scale, *EXPECT-SF* Expectations for complementary and alternative medicine treatments short form, *NRS* Numerical rating scale, *RLP* Residual limb pain, *PLP* Phantom limb pain, *PGIC* Patients’ global impression of change

### Assignment of intervention

#### Sample size

Sample size calculation is based on previous studies investigating the surgical treatments for neuroma pain [12, 13] and based on the limited number of available participants. To receive a minimum power of 80% from a Fisher’s non-parametric permutation test assuming a standard deviation of TMR and RPNI to be 2.2 and 3.3 for control [12] with a mean difference of 2.0 and at 5% significant level between the randomised groups in an allocation ratio of 2:1 (TMR and RPNI vs control), it is estimated that at least 84 (*n* = 28 per group) participants are required. With the same assumptions, but instead looking at one reconstruction technique compared to control in a ratio of 1:1 (TMR vs control, RPNI vs control), 99 participants (*n* = 33 per group) are needed to reach minimum power of 80% with a Fisher’s non-parametric permutation test with a mean difference of 2 NRS and at 5% significant level. The drop-out rate is expected to be around 10%; therefore, a total of 110 participants will be aimed to be randomised.

## Randomisation

Participants will be assigned to either of the three treatments according to the optimal allocation scheme of minimisation that aims at reducing the imbalance between the number of participants allocated to each treatment group. The randomisation proportion aims to be 1:1:1, with the same number of major limb amputations assigned to each group. The allocation aims to minimise the imbalance of the following factors:Level of amputation (upper and lower)Baseline residual limb pain based on the NRS (medium 4–6 and high 7–10)Investigation site (Sweden, Italy, Canada, Chile, Australia, UK, and USA)

The clinical randomisation of the participants will be performed using the randomisation module in REDCap [31], a tool for electronic capturing of research data. When a new recruitment is made at a site, and the participant meets the study criteria and the minimising factors of the participant are embedded in the software. The software will run a randomisation and allocate the participant to one of the treatment groups and a pseudonym code will be automatically assigned to the study participant.

### Blinding

The study is designed so that the participant and the evaluator are blinded to the surgical treatment the participant has received. The participants will undergo the same study-specific assessments despite their assigned surgical treatment. The only difference between the groups will be the surgical treatment, although the participants in the RPNI group will have an additional scar on the muscle donor site (inconceivable to the participant) compared to the TMR and neuroma transposition group. The participants will not have any expectation of surgical outcome superiority since the trial will be communicated as a comparison between three surgical treatments formerly described in the literature. The evaluator and the participant will be unaware of which surgical treatment the participant has received up to 12 months post-surgery. Thereafter, the study will be unblinded for the participants and the evaluator. The clinical investigator in each site will be aware of the treatment allocation, and they are excluded from the analyses. The raw data following the outcome assessments from each surgical treatment will have the same structure, which make it unfeasible to differentiate the group assignments without having the document that links the specific treatments to participants’ code numbers.

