**Methods:**

One hundred ten upper and lower limb amputees suffering from RLP will be recruited and assigned randomly to one of the surgical interventions (TMR, RPNI, or neuroma transposition) in an equal allocation ratio. Complete evaluations will be performed during a baseline period prior to the surgical intervention, and follow-ups will be conducted in short term (1, 3, 6, and 12 months post-surgery) and in long term (2 and 4 years post-surgery). After the 12-month follow-up, the study will be unblinded for the evaluator and the participants. If the participant is unsatisfied with the outcome of the treatment at that time, further treatment including one of the other procedures will be discussed in consultation with the clinical investigator at that site.

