**Fig. 2 Fig2:**
[figure not shown]
Study flowchart of the double-blind, randomised controlled trial. One hundred ten lower and upper amputees are recruited and randomly assigned to one of the surgical treatments for postamputation pain in an equal allocation ratio. The follow-up is short term (1 to 12 months post-surgery) as well as long term (2 and 4 years post-surgery). The study will be unblinded 12 months post-surgery, where treatment outcomes will be discussed in consultation with the clinical investigator at the site

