## Data Availability

The clinical investigators and the principal investigator have full access to all study-specific data, except for the document including the link between surgical treatment and participant’s code number. That document will only be accessible after the 1-year follow-up analyses. They have the responsibility for correct data storing and for the accuracy of the data analysis.

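### Evaluator unblinding at 12 months would overlap with later participants' primary ratings, and it does not fit the rule on the linking document

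*Protocol article*

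**What the plan says.** **When blinding ends.** Blinding: "The evaluator and the participant will be unaware of which surgical treatment the participant has received up to 12 months post-surgery". The next sentence reads: "Thereafter, the study will be unblinded for the participants and the evaluator". The Fig. 2 legend puts it this way: "The study will be unblinded 12 months post-surgery, where treatment outcomes will be discussed in consultation with the clinical investigator at the site". The Abstract (Methods) links the same moment to a discussion of further treatment, which may include one of the other procedures: "If the participant is unsatisfied with the outcome of the treatment at that time". Trial design says much the same.

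**When the key opens.** Data Availability says that the clinical investigators and the principal investigator "have full access to all study-specific data, except for the document including the link between surgical treatment and" code number. It adds: "That document will only be accessible after the 1-year follow-up analyses".

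**Who analyses.** Blinding: "The clinical investigator in each site will be aware of the treatment allocation, and they are excluded from the analyses". Data Availability, of the clinical investigators and the principal investigator together: "They have the responsibility for correct data storing and for the accuracy of the data analysis".

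**Who rates, and over what period.** Data collection and management has an evaluator at each site who oversees the case report forms and documents outcomes during the trial. Trial status expects recruitment to start in early 2023 and finish in 2025. The article does not provide a separate evaluator for later participants, and it does not delay the evaluator's unblinding until the last 12-month visit.

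**The concern.** If the evaluator is told each allocation once that participant reaches 12 months, then from the first such visit onward the site is rated by someone who knows some allocations. That person still has later participants' primary ratings to collect. The outcomes are subjective, as the Discussion acknowledges, and the trial presents itself as double-blind.

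Three indirect routes could let this knowledge affect later ratings:

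- Allocation is by minimisation with investigation site as a factor (Randomisation), so known past allocations make later ones somewhat easier to guess.
- An evaluator who has seen outcomes alongside allocations may form expectations about the techniques.
- Neuroma pain, a secondary outcome, is elicited by physical stimulation such as digital pressure, so the manner of assessment could matter.

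Separately, the coded data are meant to be uninformative without the linking document. Telling the evaluator, who oversees the code-numbered case report forms, each allocation would partly recreate that document at the site before the analysis.

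**Working it through.** No planned figure is in dispute. The target of 110 follows from 99 evaluable participants and 10% drop-out (99 / 0.90 = 110) and is unaffected. The check compares the passages under each reading and then estimates the overlap in time.

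**Two readings of the unblinding sentence**

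| Reading | Abstract, Trial design, Fig. 2 (12-month consultation) | Data Availability (key closed until after one-year analyses) |
|---|---|---|
| Each participant's own 12 months | Fits | Sits badly: evaluators hold allocations before the analyses |
| Whole study at once, after the last 12-month visit | Fails for nearly everyone: early participants wait far beyond 12 months | Fits |

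The clock is counted from surgery and the consultation takes place at that time, so the first reading is the more natural. Neither reading satisfies every section as written.

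**Inputs for the timeline**

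- 110 participants and 9 hospitals (Trial design): 110 / 9 = 12.2, so about 12 per hospital. An even spread is an assumption.
- Accrual from early 2023 to 2025 (Trial status). The months are not given, so T = 24 to 36 months is assumed, with uniform entry and surgery at entry.
- One evaluator per site throughout (Data collection and management).

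**Per-participant reading**

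1. Primary ratings made after the site's first unblinding: everyone but the first participant, (12 − 1) / 12 = 11/12, or 92%. This does not depend on T.
2. Share with surgery after the site's first unblinding. If the site's first surgery is at month m, this is (11/12) × [1 − 12 / (T − m)], and the expected m is T/13.
   - T = 24: m = 1.85, so (11/12) × (1 − 12/22.15) = 0.42.
   - T = 36: m = 2.77, so (11/12) × (1 − 12/33.23) = 0.59.
   - Averaging over m by simulation gives 42% and 58%.
3. The same share counted trial-wide from the first participant anywhere, (T − 12) / T: 12/24 = 50% and 24/36 = 67%.

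**Study-wide reading**

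A participant entering at time t waits T − t beyond their own 12-month visit. The mean is T/2 = 12 to 18 months and the maximum is T = 24 to 36 months, plus analysis time. That cannot be squared with unblinding at the 12-month consultation.

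The shares in steps 1 to 3 measure exposure to knowledge of other participants' allocations. They do not measure bias.

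**The case against.** A reader might infer more than the document supports, and several counter-arguments stand.

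- **That evaluators know the allocation of the person they are rating.** They do not. Blinding is defined for each participant, and a later participant's allocation stays concealed until that participant's own 12 months. Knowing earlier allocations helps only indirectly.
- **That the primary outcome is directly exposed.** The primary outcome is residual limb pain on a self-reported NRS, and the section on distinguishing pain types rules out physical stimulation for it. Evaluator-elicited pain concerns a secondary outcome.
- **That the donor-site scar makes early unblinding decisive.** Blinding and the Discussion both disclose the additional scar in the RPNI group. An evaluator who saw it and knew the procedures could suspect RPNI under any unblinding rule. The article does not say that evaluators see the donor site.
- **That the 12-month consultation and the closed key are strictly incompatible.** They are not. The clinical investigator already knows the allocation and can tell the participant without opening the linking document. The difficulty lies in unblinding the evaluator.
- **That the two statements about clinical investigators flatly contradict each other.** Being kept out of the analyses may refer to conducting them, and responsibility for accuracy may refer to accountability. Their data access also carries an explicit exception for the linking document. Withholding that document from people who know allocations makes sense if each knows only their own site's. The text does not say which meaning is intended, so it needs rewording, but it does not show that unblinded people will run the analysis.
- **That investigators should lose all access to outcomes, or that evaluators should stay blind to four years.** Investigators record adverse events at each visit and discuss unsatisfactory outcomes at 12 months, so they need access. Once participants know their allocation, self-reported scores at two and four years are open-label, and a blinded evaluator would add little.

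Per-participant unblinding is itself an inference, since the text speaks of the study being unblinded. The ambiguity is still a defect, because each reading conflicts with some other section.

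**Conclusion.** The point holds in limited form. As written, the unblinding rule most naturally reveals earlier allocations to site evaluators while later primary ratings are still being collected, and this sits badly with a linking document that stays closed until the one-year analyses are finished. The study-wide reading cures that but defeats the 12-month consultation.

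On the per-participant reading, 11 of 12 primary ratings at a typical site come after the evaluator's first unblinding, and about 42% to 58% of a site's participants would have surgery after it. These figures assume even accrual over 24 to 36 months, about 12 participants per hospital and one evaluator per site. The resulting bias is indirect and cannot be quantified from the document, and the self-reported primary outcome limits it. The change is worth making because it is cheap and protects the double-blind claim. The document does not show that blinding of the primary outcome has failed.

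**What to change.** State one rule in Blinding and use it in the Abstract, Trial design, the Fig. 2 legend and Data Availability:

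1. After a participant's 12-month ratings are recorded, the clinical investigator, who already knows the allocation, informs that participant only.
2. Evaluators and analysts remain blinded, and the linking document remains closed, until the last participant's 12-month visit and database lock.
3. Reword Data Availability so that clinical investigators, who know their own site's allocations, do not conduct the primary analysis, in line with Blinding. They keep the access needed for adverse events and the 12-month consultation. Say who does conduct the analysis and who is accountable for it.

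The cost is protocol wording and matching access rights. No extra staff are needed, because the clinical investigator already knows the allocation and already takes part in the 12-month consultation. No visit, treatment or sample size changes. The one practical burden is keeping evaluators from learning allocations at or after that consultation, for example from participants who have just been told.

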## Data collection, management, and analysis

### Data collection and management

The clinical investigators and the principal investigator will share the overall responsibility for the progress of the RCT. The trial coordinator will be in charge of ensuring that the RCT is conducted, recorded, and reported according to the clinical protocols, Good Clinical Practise (GCP), and regulatory requirements. The study will be monitored twice a year by a project independent monitor educated in GCP.

The evaluator at each site will oversee the case report forms (CRFs) and documents the outcomes during the RCT. The data in the CRFs will be identified by participant-specific code numbers. Data documentation will also be applicable for participants who have given written consent for participation, then underwent the baseline assessments but decided to leave the study. In the CRF, all items must be filled in, none must be empty. However, if data is missing or is unfeasible to collect, this should be documented as “not available” (NA), and an explanation must be recorded in the CRF.

The clinical investigator at each site will be in charge of recording any occurrences of adverse events (AE), in discussion with the participant at each visit, and documentation of the AE in the participant’s CRF. Every AE needs to be explained by duration (start and stop dates and times), severity, outcome, treatment, and relation to the surgical treatment (related or unrelated). The clinical investigator must report any incidence of an AE to the principal investigator and the trial coordinator in a timely manner (no later than three working days after the incident).

The data collected in this study will include images, sound recordings, questionnaires and interview answers, and medical data. Images and sound recordings will only be shared with the written consent of the participant. Participants will be able to choose whether images can be shown undoctored or with their faces blurred or cropped out. All data will be pseudonymised with a code consisting of two letters and three digits and all collected data will be assigned the coded identity.

All data gathered within this RCT will be stored digitally in accordance with GDPR requirements, on a password-protected server with restricted access using two-factor authorisation. Only the researchers who are directly involved in the study will have access to the data. The principal investigator will ensure that all relevant research personnel have access to the data. The document which couples the surgical technique that the study participant received to their unique code will be password-protected and saved separately. All information will be confidential and stored in accordance with GDPR and with the study participant’s written informed consent.

### Statistical analyses

The statistical analyses will be performed pairwise comparing the techniques in the following scheme:Reconstruction techniques compared to control: TMR and RPNI vs control (2:1)Individual comparison of each reconstruction technique compared to the control: TMR vs control (1:1) and RPNI vs control (1:1)Comparison between the reconstructive techniques: TMR vs RPNI (1:1)

Statistical analysis for the primary outcome, the mean difference of change in NRS score (0–10) of residual limb pain between baseline and 1-year follow-up between the two reconstructive surgical methods and control (2:1), will be performed with an ANCOVA for comparison of independent means on ITT population at 5% significance level, adjusted for the stratification (minimisation) variables NRS pain at baseline, level of amputation, and site. Imputation will be performed with the last observation carried forward (LOCF). A sensitivity analysis will be performed using a two-sided non-parametric permutation test for comparison of independent means on the ITT population. A complementary analysis will be performed for the primary variable of the PP population. The main results will be the mean difference with 95% CI, effect size, and *p*-value.

Secondary analyses will be performed unadjusted, between the two groups on both ITT and PP-population with Fisher’s non-parametric permutation tests for continuous variables, with the Mantel–Haenszel chi-square test for ordered categorical variables, and with Fisher’s exact test for dichotomous variables and performed adjusted with ANCOVA for continuous variables and with multivariable logistic regression for dichotomous variables.

Exploratory analyses will be performed to investigate the differences in groups such as lower vs upper extremity, right vs left extremity, female vs male, reason for amputation, baseline NRS (medium 4–6, high 7–10), time since amputation, and age. These exploratory analyses will be done within each group and then pooled together. All significance tests will be two-sided and conducted at the 5% significance level. When half of the study population has passed the 1-year follow-up, an independent committee including a medical expert and a statistician will examine the data with regard to safety.

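### If the planning SDs hold, the primary 2:1 ANCOVA and its permutation check, both in ordinary form, would be anti-conservative (type I error up to about 8–8.7%)

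*Protocol article*

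**What the plan says.** In the Protocol article, Statistical analyses, the primary outcome is the change in residual limb pain NRS from baseline to one year. The two reconstructive techniques together are compared with control (2:1), and the analysis "will be performed with an ANCOVA for comparison of independent means on ITT population at 5% significance level", adjusted for baseline NRS, amputation level and site. Missing values are filled by LOCF. The mean difference with 95% CI, an effect size and a p-value are the main results. The check on method is described as follows: "A sensitivity analysis will be performed using a two-sided non-parametric permutation test for comparison of independent means on the ITT population".

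The Sample size section plans on unequal spread, "assuming a standard deviation of TMR and RPNI to be 2.2 and 3.3 for control", "with a mean difference of 2.0 and at 5% significant level between the randomised groups in an allocation ratio of 2:1". The Trial design section gives 37 per group, so the primary contrast is about 74 against 37. Nothing in the article mentions unequal variances in the analysis, a robust or Welch-type standard error, or a studentised permutation statistic.

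**The concern.** The usual ANCOVA estimates one residual variance for everyone. When groups are unequal in size and the smaller one varies more, that estimate is dominated by the larger, less variable group. The standard error of the difference is then too small. Permuting labels on a raw mean difference has the same weakness, because the reference distribution mixes the two spreads.

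At stake are the p-value and the interval that the article names as main results. With equal means and unequal spread, the test would declare a difference more often than 5% of the time. The interval would under-cover whether or not the means differ. Because the sensitivity analysis shares the weakness, its agreement with the primary result would give no reassurance on this point.

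**Working it through.** **Inputs.** SD 2.2 (TMR, RPNI) and 3.3 (control), difference 2.0, two-sided 5%, power 80%, and stated sizes 84, 99 and 110 (Sample size); 37 per group (Trial design); ANCOVA covariates and permutation test (Statistical analyses).

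**The plan's own figures.**
- 2:1 contrast. The unequal-variance normal formula gives n_control = (1.960 + 0.842)² × (3.3² + 2.2²/2) / 2² = 26.1, so 27. Simulated Welch power is 79.0% at 54:27 and 80.7% at 56:28. The stated 84 therefore reproduces as an unequal-variance calculation. The permutation test that the section names has about 88% power at 56:28 and reaches 80% at about 46:23 (69 in total).
- 1:1 contrasts. At 33:33, permutation power is 81.2%, so 99 reproduces.
- Drop-out. 99 / 0.9 = 110.

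**Standard error at 74:37.**
- Pooled variance = (73 × 4.84 + 36 × 10.89) / 109 = 6.84.
- Pooled SE = √[6.84 × (1/74 + 1/37)] = 0.527.
- True SE = √(4.84/74 + 10.89/37) = 0.600.
- Ratio = 0.527 / 0.600 = 0.878.

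**Type I error, equal means.** The closed form 2 × [1 − Φ(c × 0.878)] gives 8.2% with the t critical value on 109 df and 8.5% with c = 1.96. Simulation with normal outcomes at SDs 2.2 / 3.3 gives:

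| Method | 74:37 | 66:33 |
|---|---|---|
| Pooled t | 8.5% | 8.4% |
| ANCOVA (baseline, level, 7 sites), common variance | 8.3–8.5% | 8.2% |
| Permutation, raw mean difference | 8.2% | 8.4% |
| Welch t | 5.05% | 5.1% |
| ANCOVA, HC3 SE | 4.4% | 4.3% |
| Permutation, studentised | 5.2% | 4.8% |

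A separate simulation at 74:37 gave 8.7% for the common-variance ANCOVA and 4.6% with HC3. Baseline correlations from 0 to 0.6 made no material difference. Because 110 does not divide by three, 73:37 was also run and gave 8.3% for the ANCOVA.

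**Controls.** The same ANCOVA at 74:37 with equal SDs gives 5.0–5.1%. With SDs 2.2 / 3.3 at 37:37 it gives 4.8%, and the pooled t gives 5.0%. At 37:37 the pooled and true SEs are both 0.652. The excess therefore needs unequal spread and unequal group sizes together.

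**Sensitivity to the SD ratio (closed form, 74:37).** The type I error is 4.8% at a ratio of 1.0 (nominal, allowing for the approximation), 5.5% at 1.1, 6.6% at 1.25, 8.2% at 1.5 and 9.5% at 1.75. If the TMR and RPNI means lie 1 NRS point either side of their pooled mean, the reconstructive group's spread widens and the error at the planning SDs falls to about 6.7–6.9%.

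**The case against.** The strongest reply is that the article specifies neither a pooled residual variance nor the permutation statistic. Both can be left to an analysis plan that is not shown here. This stands as a limit: the point holds only for the named methods in their ordinary form. It does not remove the point, because the article itself assumes unequal SDs, names the model and the sensitivity test, and signals no allowance for unequal spread in either.

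Second, the SDs are planning values from a cited earlier trial that, according to the Discussion, had 28 participants. Assuming 14 per arm (the split is not given), 3.3 against 2.2 has an F-test p of about 0.16 and a 95% interval for the SD ratio of about 0.85 to 2.65. Equal variances are compatible with that source. This stands, and it is why a range is needed.

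Third, if the choice of surgery changed nobody's outcome, the distributions would be identical and the permutation test would hold its 5%. This also stands. The inflation concerns equal means with unequal spread. That case is still relevant, because the article reports a mean difference with an interval and plans on unequal spread.

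A reader might go further and infer that the trial's true error rate is 8%, that the permutation test is invalid, or that the sample size is wrong. The documents support none of these. The first depends on an SD ratio that is not yet known. The second fails under the strict null. The stated sizes all reproduce.

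**Conclusion.** The concern holds in conditional form and is a should-fix. With a common-variance ANCOVA and a raw mean-difference permutation test, the primary 2:1 contrast would have a type I error of about 8–8.7% and interval coverage of about 91.5–92% under the protocol's planning SDs.

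This rests on four assumptions: the SD ratio of 1.5 carries over to the residuals, the null is equal means with unequal spread, TMR and RPNI share the same mean, and outcomes are roughly normal. A smaller ratio brings the error towards nominal. The 1:1 comparisons are not affected.

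The inconsistency lies between sizing and testing. The stated 84 matches a calculation that allows for unequal variances, while neither named test does so in its ordinary form.

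**What to change.** Keep the ANCOVA and its covariates. Before unblinding, pre-specify for the 2:1 comparison either a heteroscedasticity-consistent SE (HC2 or HC3) or arm-specific residual variances with Satterthwaite degrees of freedom, and base the CI and p-value on it. Use a studentised (Welch) statistic in the permutation sensitivity test. Choosing the variance estimator after unblinding would be open to challenge as data-driven.

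The cost is wording and a somewhat wider interval; no extra participants are needed. HC3 is slightly conservative: about 4–4.6% in these runs, including 4.1% when the SDs are equal. Power for a 2.0-point difference with HC3 is about 83% at 66:33 (completers only) and 87% at 74:37 (all randomised, as LOCF implies). Both exceed the stated 80%. HC2 and the arm-specific variance model were not simulated. If a site contributes a single participant, its leverage is 1 and HC2 and HC3 cannot be computed as they stand, so a rule for merging very small sites should be written down with the estimator.
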